## **Interventions**

#### **Intervention A (addendum for operational protocol)**

The intervention will include key elements of proven efficacy for health promotion combined and adapted to each community through a co-design and co-creation process, involving service providers and end-users.

Stakeholders will include professionals involved in diabetes care and providing services to hard-to-reach populations, immigrants with diabetes (the final user), relevant people of the communities and professionals of the third sector. A combination of different methodologies (focus group, consultations, stakeholder meetings, and qualitative interviews among the others) will be used by each centre to co-create a community-tailored intervention [Leask CF 2019] adapted to the local context of each centre with a different implementation of key elements:

- a) Dietary habit: the key elements will be theoretical dissemination of information on healthy diet (i.e. cookbooks with healthy and easy-to-make recipes), and courses on healthy cooking targeted to family and factory cooks (i.e. how to cook healthy dishes respecting the preferences and the taste of the community of origin, but feasible with ingredients available in the hosting region).
- b) Physical activity: the key elements will be the promotion of organized physical activity compatible with the daily time restrictions of the patients, promotion of non-organized physical activity (i.e. analysing the possibilities of moving home-work on foot or by bicycle and using an opportunity map that shows parks and possibilities for spontaneous physical

activity), theoretical dissemination of information on adapted physical activity (i.e. lectures with sports instructors or healthcare professional with specific expertise). Use of apps to measure physical activity will be considered.

- c) Adherence to treatments: tools favouring compliance and glucose measuring, as well as culture-tailored information material on diabetes and its health implications will be used.

The intervention will last a minimum of 3 months and will include at least one individual counselling (IC), one family session, and at least two group sessions (FS) for dietary and physical activity courses. Mandatory elements for the intervention and a non-exhaustive list of optional elements, as well as, elements that can be modulated in the co-creation phase are reported by topic in Table 1.

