### Sample size

To explore the efficacy of a culturally adapted diabetes education model in improving health literacy and self-care (primary endpoint) in immigrant patients with type 2 diabetes. The intervention is expected to provide a 0.5% higher reduction in the concentration of HbA1c compared to the usual care at a 12-month follow-up, with a positive effect on the risk of CVD events (Selvin 2004; Mitsios 2018). Through a change in health-related behaviours, it is also expected to reduce overweight and increase vegetable intake and physical activity, with a positive impact on future risk of non-communicable diseases and quality of life (GBD 2019 Risk Factors Collaborators 2020). To have a power of 80%, considering an alpha of 0.05 (Islam 2013), in order to detect a minimum significant reduction of 0.5% in the glycated haemoglobin in the intervention group compared to the control group at least 200 participants are needed (considering a SD in both group of 1.3) (Bellary 2008).

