#### **Intervention assignment**

Block randomization (1:1 ratio) will be computerized and conducted in each centre to balance the ethnic composition of the intervention and control groups. Members of the same household, whether identified as cohabitant during the recruitment visit, will be assigned at the same arm.

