#### **Statistical plan**

Descriptive statistics will be calculated for baseline characteristics. The analysis will be intention-to-treat. Before/after variations of the glycated haemoglobin, lipid profile and renal function biomarkers, and anthropometric measure will be computed and standardized if opportune. Paired and unpaired tests will be used to assess the effects of the intervention and to analyse before/after within-group and between-group differences and changes in glycated haemoglobin. Changes in lifestyle habits (both related to diet and physical activities) will be described in terms of positive or negative changes.

Linear regression models will be used to analyse the variation of anthropometric measures and assessed biomarkers.

Multilevel linear models will be performed taking into account the influence of the centre on intervention efficacy.

We will perform a mediation analysis to understand which part of the changes in outcomes (glycated haemoglobin, lipid profile, and anthropometric measures) is attributable to changes in

physical activity, changes in diet, adherence to therapies, and other direct or unmeasured effects of the intervention.

The statistician will not be blinded to group assignments.

The statistical significance level will be set at 5%, and all analyses will be performed by using Stata 16 or SPSS 28.

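### Cohabiting participants are assigned to the same arm, but none of the analyses named in the protocol accounts for household

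*Protocol*

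**What the plan says.** **Assignment.** Under Intervention assignment, the protocol plans "Block randomization (1:1 ratio) will be computerized and conducted in each centre" and then adds: "Members of the same household, whether identified as cohabitant during the recruitment visit, will be assigned at the same arm". A patient living alone, or the first of a household to enrol, is randomised individually. A recognised cohabitant takes the arm of the household.

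**Analysis.** The Statistical plan names paired and unpaired tests for HbA1c and linear regression for anthropometric measures and biomarkers. It then states: "Multilevel linear models will be performed taking into account the influence of the centre on intervention efficacy". Centre is the only grouping factor it mentions. Household, clustered or robust variance and within-household correlation appear nowhere in the protocol.

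**Sample size.** The calculation is a plain comparison of two means: "To have a power of 80%, considering an alpha of 0.05", a difference of 0.5% HbA1c, "considering a SD in both group of 1.3", and the result "at least 200 participants are needed". It includes no design effect.

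**Data flow.** Under Data management, each participant receives a pseudonymised code that specifies the recruiting centre. The datasets then go to a separate centre for analysis. The section mentions no household identifier.

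**Delivery.** Under Intervention A, the intervention arm receives individual counselling, a family session and at least two group sessions. Under Intervention B, controls receive usual care, with no group sessions named.

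**The concern.** The analysis should respect the unit that was randomised. Two cohabitants who are always in the same arm do not contribute two independent observations to the comparison between arms. They probably share meals, cooking and daily routine, which are what this intervention tries to change, so their HbA1c changes may well be correlated whatever arm they are in. A term for centre does not remove that correlation, because the two are alike beyond being in the same centre.

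At stake are the width of the confidence interval for the primary endpoint and the true level of its 5% test. There is also a practical risk. If the dataset reaches the analysing centre without a household identifier, the statistician cannot make the correction there.

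The rule that keeps cohabitants together is not itself at fault. Only the analysis does not follow from it.

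**Working it through.** **1. Inputs from the protocol.** Difference 0.5, SD 1.3, alpha 0.05 (sidedness not stated; two-sided assumed), power 80%, total 200, ratio 1:1.

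**2. The plan's own figure, for independent patients.** Per arm, n = 2 × (SD × (z₀.₉₇₅ + z₀.₈₀) / difference)² = 2 × (1.3 × (1.960 + 0.842) / 0.5)² = 106.1. This rounds up to 107 per arm, or 214 in total. With 100 per arm the power is Φ(0.5 / (1.3 × √(2/100)) − 1.960) = 77.6%. The stated 200 is therefore slightly short even without clustering. That is a separate point, but it means there is no reserve for a design effect.

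**3. Inputs that must be assumed.** The protocol does not give f, the share of patients in two-patient households, or r, the within-household correlation of HbA1c change. The range used is f = 5% to 40% and r = 0.3 to 0.5.

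**4. Variance inflation.** In an arm of n patients there are nf/2 pairs. The variance of the sum is nσ² + 2 × (nf/2) × rσ² = nσ²(1 + fr). The design effect is V = 1 + fr in both arms, and the true standard error is √V times the one that ignores household.

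**5. True level and power.** Type I error of the test that ignores household = 2 × (1 − Φ(1.960/√V)). Power at 200, with correct standard errors, = Φ(0.5 / (1.3 × √(2V/100)) − 1.960). Total for 80% power = 2 × 106.1 × V, rounded up within each arm.

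| f | r | V | SE ratio | Type I error | Power at 200 | Total for 80% |
|---|---|---|---|---|---|---|
| 0 | – | 1.000 | 1.000 | 5.00% | 77.6% | 214 |
| 5% | 0.3 | 1.015 | 1.007 | 5.17% | 77.0% | 216 |
| 5% | 0.5 | 1.025 | 1.012 | 5.29% | 76.6% | 218 |
| 10% | 0.3 | 1.030 | 1.015 | 5.35% | 76.4% | 220 |
| 10% | 0.5 | 1.050 | 1.025 | 5.58% | 75.6% | 224 |
| 20% | 0.3 | 1.060 | 1.030 | 5.70% | 75.2% | 226 |
| 20% | 0.5 | 1.100 | 1.049 | 6.17% | 73.7% | 234 |
| 40% | 0.3 | 1.120 | 1.058 | 6.40% | 72.9% | 238 |
| 40% | 0.5 | 1.200 | 1.095 | 7.36% | 69.9% | 256 |

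**6. Where in this range the trial is likely to fall.** A pair needs two cohabiting adults who both meet the criteria: immigrant status, and type 2 diabetes newly diagnosed or with HbA1c above 8%. Both must consent within a four-month enrolment period and be recognised as cohabitants. Few patients are likely to qualify in this way. At f = 5% to 10% and r = 0.3, the type I error is 5.17% to 5.35%.

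**7. Direction.** Unmodelled positive correlation leaves the estimated difference unbiased. It widens the true sampling distribution symmetrically, so false positives rise equally on both sides.

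**The case against.** **The effect is small.** This stands. At the likely frequencies the standard error is understated by one or two percent. The upper rows of the table need 40% of patients in pairs, which nothing in the protocol suggests.

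**An offset exists.** This stands in part. Randomisation is within centre, so an unpaired test that ignores centre tends to overstate the standard error if centres differ. That works against the household effect, by an amount the protocol does not allow one to calculate. The multilevel model for centre has no such offset.

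**Variance estimation belongs in the SAP, which is not shown.** This stands in part. The protocol does not say that centre is the only level or rule out a household term, and a SAP could add one. But the protocol itself sets the household rule and names its tests, and those tests do not follow from the rule.

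**Stronger readings.** A reader might infer that the test is tilted towards the intervention. Point 7 of the working shows why it is not: the liberality is two-sided.

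A reader might also infer that the family and group sessions make the error much larger. The protocol does not support that. It gives no group size, no fixed membership and no correlation. A family session may involve one participant and relatives outside the trial. Sessions follow randomisation, so if the intervention affects nobody they create no correlation through treatment. An inflated type I error from this source needs real group-specific effects that average to zero. Because only the intervention arm has planned group sessions, a sensitivity analysis is reasonable, but a claim about size is not.

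**Conclusion.** The point holds in a limited form. The assignment rule and the named analyses do not match wherever cohabitants enrol. Analyses that ignore household then understate the standard error, provided the within-household correlation is positive and is not cancelled by the omission of centre in an unpaired test. Under the assumed ranges the design effect is about 1.015 to 1.20 and the type I error about 5.2% to 7.4%, probably near the low end. This should be fixed because the correction costs almost nothing and may be impossible later without the identifier. At its likely size it does not put the trial's conclusion in serious doubt.

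**What to change.** 1. State that the household is the unit of randomisation, with a patient who has no enrolled cohabitant counted as a household of one.
2. Record a household identifier in the CRF and include it, pseudonymised, in the dataset sent to the analysing centre. Cohabitants must already be identified at recruitment to apply the assignment rule.
3. In the primary centre-adjusted model of HbA1c change, use household-clustered robust standard errors. These suit this setting better than a household random intercept. With 10% of 200 patients in pairs there are only 10 pairs to estimate a household variance, whereas even with 40% in pairs there are 40 + 120 = 160 clusters.
4. Optionally, record a session-group identifier and run, as a sensitivity analysis, a partially nested model with a group effect in the intervention arm only.

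**Cost.** One identifier field, or two with the optional step, a sentence or two in the Statistical plan, and slightly wider confidence intervals.

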#### **Blinding (addendum for operational protocol)**

The randomization arm will not be masked to the participant nor to the investigator. The person who enrolls will be blinded to the random sequence until each patient will sign the informed consent (allocation concealment).

#### **Data processing and conservation (addendum for operational protocol)**

##### **Data collection**

The clinical information will be locally collected using the GDPR Compliant electronic platforms adopted by the recruiting centres for collecting clinical data allowing randomization.

Periodic monthly monitoring of recruitment, randomization procedures and follow-up will be collected on aggregated data reporting: number of patient contacted, refusal to participate (by sex and community), randomization (by gender, community and age group <50 and >50), presence at follow up visit.

Biomarkers will be assessed through analysis of blood and urine samples collected following standard procedures of the Diabetes clinics and analysed for glycaemia, by the authorised clinical laboratories of each recruiting centre.

Questionnaires used to assess dietary habits and physical activity will be the Mediterranean Diet Score, (MedDietScore) (Panagiotakos 2007) and the International Physical Activity Questionnaire - Short Form, IPAQ-SF. (Mannocci 2010)

Anthropometric measures will be collected following standard procedures during routine visits in Diabetes clinics with validated weight and height scales and bioelectrical impedance analysis (BIA). Therapeutic adherence will be assessed at baseline and follow up visits using the Diabetes Mellitus Treatment Adherence Scale (DMTAS). (Hou 2021)

##### **Data management**

Data will be entered with manual data entry on GDPR-compliant digital platforms as in use in the recruiting centres. The personal information will be stored locally and will be subject to technical

and organizational safeguards. For each participating subject, the system will generate a pseudo-anonymization code with the specification of the recruitment centre, as no individual can be identified without reference to personal information. This code will be present in each record relating to the same participant in the various tables of the CRF. Each centre will carry out quality controls of the data entered through crosschecks with the information present in the original sources (paper questionnaires, medical records).

Pseudo-anonymised datasets will be sent by each recruiting centre to the centre which will perform statistical analysis (Azienda USL-IRCCS di Reggio Emilia) according to the procedures reported in the Data Transfer Agreement at the end of the recruitment end follow-up.

The final analysis will be carried out when the 12-month follow-up will be available for all participants.

#### **Data retention**

Each local Principal Investigator will be responsible for data management in participating centre while the study Principal Investigator will be responsible for data management at a central level. In the recruiting centres, the data will be stored on separate files with the relative linkage key in reserved areas protected by passwords as per company procedures; the data will be kept for 20 years. The pseudo-anonymized data will be kept for 20 years in the coordinating centre.

The centres will apply the procedures for conducting clinical studies envisaged by local IT services and evaluated by local Data Protection Officers.

#### **Protocol deviations**

Substantial changes to the protocol will be submitted for evaluation by the ethics committee of the coordinating centre and then transmitted to the local ethics committees.

#### **Statistical plan**

Descriptive statistics will be calculated for baseline characteristics. The analysis will be intention-to-treat. Before/after variations of the glycated haemoglobin, lipid profile and renal function biomarkers, and anthropometric measure will be computed and standardized if opportune. Paired and unpaired tests will be used to assess the effects of the intervention and to analyse before/after within-group and between-group differences and changes in glycated haemoglobin. Changes in lifestyle habits (both related to diet and physical activities) will be described in terms of positive or negative changes.

Linear regression models will be used to analyse the variation of anthropometric measures and assessed biomarkers.

Multilevel linear models will be performed taking into account the influence of the centre on intervention efficacy.

We will perform a mediation analysis to understand which part of the changes in outcomes (glycated haemoglobin, lipid profile, and anthropometric measures) is attributable to changes in

physical activity, changes in diet, adherence to therapies, and other direct or unmeasured effects of the intervention.

The statistician will not be blinded to group assignments.

The statistical significance level will be set at 5%, and all analyses will be performed by using Stata 16 or SPSS 28.

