#### **Study endpoints (addendum for operational protocol)**

##### **Primary endpoint**

The primary endpoint is the change in glycated haemoglobin (HbA1c; mmol/mol) between the recruitment and the 12-month follow-up visit assessed through the collection of fasting blood and urine samples.

The difference between groups of the mean change (and standard deviation) in glycated haemoglobin will be used to assess the effectiveness of the intervention.

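### The HbA1c comparison is stated without baseline adjustment, which costs power, and paired within-arm tests are listed as assessing the intervention effect, which they cannot do

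*Protocol*

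**What the plan says.** The Primary endpoint section of the protocol defines the outcome as the change in HbA1c from recruitment to 12 months and fixes the effect measure: "The difference between groups of the mean change (and standard deviation) in glycated haemoglobin will be used to assess the effectiveness of the intervention".

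The Statistical plan section then says "Paired and unpaired tests will be used to assess the effects of the intervention and to analyse before/after within-group and between-group differences". It goes on to list linear regression for the variation in anthropometric measures and biomarkers, and multilevel linear models that allow for centre. Baseline HbA1c is not named as a covariate in any of these.

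The Sample size section aims to "detect a minimum significant reduction of 0.5% in the glycated haemoglobin in the intervention group compared to the control group", with 80% power, "considering an alpha of 0.05" and "considering a SD in both group of 1.3". It concludes that "at least 200 participants are needed". It does not say whether 1.3 is the SD of a single HbA1c value or of the change.

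Three other sections bear on the point. Inclusion criteria admits patients who are newly diagnosed or whose last HbA1c within 24 months was above 8%. Intervention B gives controls guideline-based usual care. Intervention assignment blocks the 1:1 randomisation within centre and puts identified cohabitants in the same arm.

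**The concern.** Two features of the stated analysis deserve correction.

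**Precision.** Every participant is to have HbA1c measured at baseline. A raw change score uses that value with a fixed weight of 1. A regression on baseline estimates the weight from the data and is never less precise in large samples. In a trial whose planned size already falls short of its own power target, this is a gain that needs no extra patients.

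**Paired tests.** A before/after test within the intervention arm mixes the intervention with everything else that lowers HbA1c over 12 months: treatment started after diagnosis, routine visits and regression to the mean. The Sample size section itself expects a reduction 0.5 points greater than under usual care, which suggests that some fall in controls is anticipated. Listing paired tests among those that assess the effect invites a report in which a within-arm fall is presented as evidence that the intervention worked.

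**Working it through.** **Inputs from the protocol.** Difference 0.5 percentage points, SD 1.3, alpha 0.05, power 80%, total 200 (Sample size); 1:1 allocation, hence 100 per arm (Intervention assignment).

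**Assumptions.** Two-sided test; equal SD at both visits; rho between 0.3 and 0.7; complete data; no household clustering. None of these is given in the protocol.

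**Step 1: the plan's own figure.** The standard error is 1.3 × √(2/100) = 0.184, so the standardised difference is 0.5/0.184 = 2.72. Two-sided t-test power with 198 degrees of freedom is 77% (77.6% by the normal approximation). For 80% power, n per arm = 2 × (1.960 + 0.842)² × 1.3²/0.5² = 106.1, rounded up to 107, or 214 in total. The stated 200 is not reproduced. A one-sided test does not reproduce it either (168 in total).

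**Step 2: variances.** With σ the SD of one HbA1c value:

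- change score: 2σ²(1 − rho)
- baseline-adjusted: σ²(1 − rho²)
- ratio, adjusted to change: (1 + rho)/2, which is 0.65, 0.75 and 0.85 at rho 0.3, 0.5 and 0.7

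**Step 3: power at 100 per arm if 1.3 is the SD of one value.**

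| rho | SD of change | power, raw change | adjusted SD | power, adjusted | gain (points) |
|---|---|---|---|---|---|
| 0.3 | 1.538 | 63% | 1.240 | 81% | 18 |
| 0.5 | 1.300 | 77% | 1.126 | 88% | 11 |
| 0.7 | 1.007 | 94% | 0.928 | 97% | 3 |

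**Step 4: power at 100 per arm if 1.3 is the SD of change.** The adjusted SD is 1.3 × √((1 + rho)/2).

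| rho | power, raw change | adjusted SD | power, adjusted | gain (points) |
|---|---|---|---|---|
| 0.3 | 77% | 1.048 | 92% | 15 |
| 0.5 | 77% | 1.126 | 88% | 11 |
| 0.7 | 77% | 1.199 | 84% | 6 |

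Under either reading, and throughout the assumed range of rho, the adjusted analysis exceeds 80% with 200 complete participants.

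**Step 5: paired test when the intervention does nothing.** Take 100 intervention patients, a change SD of 1.3 (assumed here) and a fall common to both arms. The standard error is 1.3/√100 = 0.13. A significant fall is found by a two-sided paired t-test at 5% with these probabilities:

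| common fall (assumed) | fall/SE | significant in intervention arm |
|---|---|---|
| 0.2 | 1.54 | 33% |
| 0.3 | 2.31 | 63% |
| 0.5 | 3.85 | 97% |

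Comparing the two paired tests does not rescue the approach. At a common fall of 0.3, the intervention arm alone is significant in 0.628 × (1 − 0.628) = 23% of trials.

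**The case against.** The case on the other side has real force on several points.

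- A reader might infer that a within-arm fall would count as success. The documents do not support that. The Primary endpoint section makes the between-group difference the measure of effectiveness, and the sentence in the Statistical plan can be read as paired tests for within-group and unpaired tests for between-group differences. What stands is that the sentence says both kinds of test assess the intervention effect, which blurs a criterion stated clearly elsewhere.
- A reader might infer that centre is ignored. It is not: multilevel models for centre are planned.
- A reader might infer that the unpaired test of change is invalid. Under randomisation it is unbiased; it is only less efficient.
- Covariates, and the choice of which listed model is primary, are often left to a statistical analysis plan, which is not shown here. Nothing in the protocol bars baseline HbA1c from the regression models. This means the absence of a covariate list is not itself the fault. The point rests on what the protocol does state as the effect measure and the tests, for which a better method is available from data already collected.
- It is tempting to say that a significant paired test is nearly certain without any effect. That holds for a common fall near 0.5 points, not for 0.2, and the protocol gives no expected fall in controls. The qualifying HbA1c may also be up to 24 months old while baseline is a new sample, so part of any regression to the mean may occur before baseline.
- The share of newly diagnosed patients is not given, so a rho below 0.5 is possible but is conjecture.

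**Conclusion.** The point holds as a worthwhile improvement, not as an error that invalidates the trial. The stated comparison of mean change is valid but leaves precision unused: its variance exceeds that of a baseline-adjusted comparison for any rho below 1. Over rho 0.3 to 0.7 the cost at 200 participants is about 3 to 18 points of power if 1.3 is the SD of one value, and about 6 to 15 points if it is the SD of change. The size within those ranges depends on a correlation and an SD definition that the protocol does not give. It matters because the stated inputs yield about 77% power before any dropout or household clustering, either of which would lower both sets of power figures.

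The paired tests cannot assess the intervention effect whatever the values of these unknowns. How often they would mislead depends on the assumed common fall and the assumed change SD.

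**What to change.** Amend the Primary endpoint and Statistical plan sections so that one between-group analysis decides the primary endpoint: a linear model of 12-month HbA1c on arm, adjusted for baseline HbA1c and for centre, reporting the adjusted difference with its 95% confidence interval. Centre can enter as fixed indicators or through the multilevel model already planned. Because identified cohabitants share an arm, add cluster-robust standard errors or a random effect for household. Adjustment for newly-diagnosed status is optional.

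The endpoint need not change: with baseline HbA1c in the model, the arm coefficient is the same whether the outcome is the 12-month value or the change.

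Use the same baseline adjustment for the continuous secondary outcomes (lipids, weight, BMI, waist circumference, blood pressure). Report within-arm changes as means with SDs only, and remove paired tests from the analyses said to assess the effect.

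The cost is a change of wording. No new data are needed, and the models can be fitted in the software that the protocol names.

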##### **Secondary endpoint**

Secondary endpoints include:

- Biomarkers related to lipid profile assessed through the collection of fasting blood samples: triglycerides (mmol/l), LDL (mmol/l), HDL (mmol/l), total Cholesterol (mmol/l), free fatty acids (mmol/l), anthropometric measures (height, weight, BMI, waist circumference) and health related behaviours.
- Anthropometric measures: weight, height and waist circumference, bioelectrical impedance analysis (BIA).
- Systolic and diastolic blood pressure.
- Physical activity and dietary habits self-reported data.
- Increase in adherence to Mediterranean Diet

- restriction of daily alcohol consumption (<160 kcal);
- compliance with WHO recommended exercise goals
- Indicators of compliance with individual therapeutic protocols in terms of number of attended visits, number of tests of renal function and glycaemic control, and drug prescription.

Blood and urine samples and anthropometric measures will be collected at baseline and 12-month follow up visits.

Physical activity and dietary habits data will be collected through a questionnaire on lifestyle, dietary habit and physical activity fulfilled by each participant during routine visits in Diabetes clinics. The questionnaires used to assess dietary habits will be the Mediterranean Diet Score, (MedDietScore).(Panagiotakos 2007) The questionnaire used to assess physical activity will be the International Physical Activity Questionnaire - Short Form, IPAQ-SF. (Mannocci 2010)

Therapeutic adherence will be assessed at baseline and follow up visits using the Diabetes Mellitus Treatment Adherence Scale (DMTAS). (Hou 2021)

Descriptive analysis of mean (or median) changes with relative SD (or IQR) and the proportion of patients reaching therapeutic/recommended targets will be used.

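### Diet and physical activity changes are described by direction in one section and by mean or median in another, and neither section explicitly plans a baseline-adjusted between-arm estimate

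*Protocol*

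**What the plan says.** Four places in the protocol bear on this.

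- **Secondary aims.** Diet and physical activity are listed among the secondary objectives, which are framed as descriptions of change.
- **Secondary endpoint.** The list includes "Physical activity and dietary habits self-reported data". The instruments are the MedDietScore ("The questionnaires used to assess dietary habits will be the Mediterranean Diet Score, (MedDietScore") and the IPAQ-SF. The section closes with its analysis: "Descriptive analysis of mean (or median) changes with relative SD (or IQR) and the proportion of patients reaching therapeutic/recommended targets will be used".
- **Statistical plan, outcomes.** Lifestyle changes, for both diet and activity, "will be described in terms of positive or negative changes". The next sentence reads "Linear regression models will be used to analyse the variation of anthropometric measures and assessed biomarkers". The one after it reads "Multilevel linear models will be performed taking into account the influence of the centre on intervention efficacy" and names no outcome.
- **Statistical plan, mediation.** A mediation analysis is to apportion the changes in HbA1c, lipids and anthropometry to changes in "physical activity, changes in diet, adherence to therapies, and other direct or unmeasured effects of the intervention". The scale on which diet and activity enter is not given.

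Both questionnaires are collected at baseline and at 12 months (Study design; Study timeline).

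**The concern.** Diet and physical activity are two of the three behaviours that the intervention addresses; the third is adherence to treatment (Primary aim; Intervention A). If HbA1c moves, readers will ask whether these behaviours moved too. If it does not, they will ask whether the intervention failed to change behaviour or whether behaviour changed without effect. Either answer needs an estimate of how far the arms differ on each score, with its uncertainty.

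The direction of change does not supply that. It counts a small shift the same as a large one. It also takes no account of baseline: a patient who starts low has more room to improve, and regression to the mean works in the same direction, so a chance imbalance at baseline can carry over into the count of improvers. The documents give no figures from which to judge how strong this would be here.

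The mediation analysis sharpens the point. It rests on the effect of the intervention on each mediator, and the plan does not state how that effect will be estimated or on what scale.

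**Working it through.** **Step 1. What each section plans for the two scores.**

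| | Secondary endpoint | Statistical plan |
|---|---|---|
| Form of the change | Mean or median, with SD or IQR; proportion reaching targets | Positive or negative |
| Named outcome of linear regression | Regression not mentioned | No; only anthropometry and biomarkers are named |
| Multilevel models | Not mentioned | Outcome not named, so neither included nor excluded |
| Mediation analysis | Not mentioned | Included as mediators, scale not stated |
| Baseline-adjusted between-arm difference | Not stated | Not stated |

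The first row is the inconsistency: the same endpoints are summarised on a numeric scale in one section and by direction in the other. The last row is the gap.

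**Step 2. Whether another sentence fills the gap.** The paired and unpaired tests in the Statistical plan open with a general reference to intervention effects, but the comparisons that the sentence goes on to name concern HbA1c. Even on a broad reading that takes in the questionnaire scores, these are tests of change without adjustment for baseline. The multilevel sentence could cover the scores, but does not say so.

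**Step 3. Whether the scores can be modelled as numbers.** The Secondary endpoint section plans means with SDs or medians with IQRs. That presupposes numeric scores at both visits, so nothing further has to be collected.

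**Step 4. What comparing arms on the sign would cost, as an assumption only.** The protocol gives no design figure for diet or activity, so there is none to reproduce. Its only power calculation is for HbA1c.

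Suppose the change is normal, with c = mean change divided by its SD. Let φ and Φ be the standard normal density and distribution function, and p = Φ(c) the share who improve. For small between-arm differences, the efficiency of comparing the share improved, relative to comparing mean change, is

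efficiency = φ(c)² / [p(1 − p)].

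- c = 0: p = 0.500; efficiency = 2/π = 0.637; loss 36%.
- c = 0.25: p = 0.599; efficiency 0.622; loss 38%.
- c = 0.5: p = 0.691; efficiency 0.581; loss 42%.
- c = 0.75: p = 0.773; efficiency 0.517; loss 48%.
- c = 1: p = 0.841; efficiency 0.439; loss 56%.

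The values of c are assumed; none is in the documents. Normality matters as well. For a Laplace-shaped change centred at zero, with scale b, the density at the centre is 1/(2b) and the variance is 2b². The efficiency is then 4 × [1/(2b)]² × 2b² = 2, so the sign would do better than the mean. The normal-theory losses are therefore not a bound for skewed or heavy-tailed scores.

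**The case against.** The strongest case on the other side has four parts.

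1. **The numeric change is kept.** The Secondary endpoint section plans mean or median changes, and if these are reported by arm, an unadjusted difference and its CI can be worked out from the means, SDs and numbers of patients. This stands. A reader might infer from the Statistical plan alone that the trial discards about a third of the information on diet and activity. The protocol does not support that, because its own endpoint section retains the numeric change.
2. **The scores are not shut out of modelling.** They are mediators, and a standard mediation analysis models each mediator on arm. The multilevel models name no outcome and so exclude none. This stands too: only the linear regression sentence omits them. But an estimate that is implied, on an unstated scale and with no stated baseline adjustment, is not a planned one.
3. **No test of the sign is planned.** The plan commits only to describing direction. A reader might put the HbA1c assumptions (0.5/1.3, a standardised difference of 0.385) into a comparison of proportions improved and quote a loss of power. That would be power for a test the protocol does not contain, with an effect size it does not give for these scores. No power figure for this trial follows.
4. **A descriptive analysis suits a descriptive aim, and adjusted models can be left to the SAP.** This has weight, and is part of why the point is minor. It does not remove it, because the protocol is not silent here: it states a method, and states it differently in two places. Some listed endpoints, such as better Mediterranean-diet adherence and meeting WHO exercise goals, are directional or target-based by nature. Reporting proportions for those is reasonable, alongside a numeric estimate.

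**Conclusion.** The point holds as a minor one, in two parts. The Statistical plan and the Secondary endpoint section describe the analysis of the same two endpoints differently. And neither explicitly plans a baseline-adjusted between-arm estimate for behaviours that the intervention targets and that the mediation analysis relies on.

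Only secondary endpoints are affected; the HbA1c analysis is untouched. No loss of information or power can be stated for this trial. The range of 36% to 56% is conditional on normal change, a mean change between 0 and 1 SD, and a comparison of arms on the sign of change. The documents supply none of these three.

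**What to change.** In the Statistical plan, state that 12-month MedDietScore and 12-month IPAQ-SF activity are analysed as numeric scores (transformed if skewed) by linear regression on arm, baseline score and centre, with the between-arm difference and its 95% CI reported for each. Keep the proportion improved as a descriptive supplement. Align the closing sentence of the Secondary endpoint section so that both sections give the same analysis.

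The cost is two more secondary models on data already collected at both visits. No visit, questionnaire or patient is added.
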